##### EMA Surveys

We will use EMA to capture the temporal dynamics of real-world affect and regulation using a probes delivered via REDCap. Each EMA survey will ask participants to complete (1) PANAS items to rate current levels of anxiety, irritability, and sadness on a 7-point Likert scale; (2) the Momentary Ruminative Self-Focus Inventory–Abbreviated [76], a 3-item questionnaire evaluating state-level fluctuations in rumination, each rated on a 7-point Likert scale; and (3) the Momentary Impulsivity Scale [77], a 4-item questionnaire measuring momentary impulsivity on a 5-point Likert-type scale. Our chief EMA emotion dysregulation indices, which we predict will decline from the preintervention assessment to the postintervention assessment, include the (1a) average levels of, and (1b) variability (ie, mean square of successive difference) in, daily negative affect (derived from mean scores on the mood probes); (2) average daily levels of rumination via the Momentary Ruminative Self-Focus Inventory–Abbreviated; and (3) average daily levels of ERI, as measured by Momentary Impulsivity Scale scores during periods of elevated momentary negative affect (ie, scores above the person-level mean).

We will provide an in-person tutorial at baseline to help familiarize participants with the structure and content of EMA surveys, and to facilitate the completion of practice items. Participants will use their personal mobile phones or other internet-capable devices to submit EMA responses. Specifically, participants will receive automatic “push” notifications to complete EMA surveys 5 times per day. We will randomize notifications by binning participants’ available waking hours into 5 equal windows and then randomly selecting a survey time within each bin, with an interval of at least 90 minutes between notifications. Surveys will be available for completion for 80 minutes, and reminder prompts will be sent within 40 minutes of missed survey notifications.

##### Questionnaires

After each in-person assessment session, we will ask participants to complete questionnaires administered via REDCap (Table 1) as promptly as possible. Each set of questionnaires includes primary and secondary outcome measures related to emotion dysregulation as well as measures of psychiatric symptom severity, perceived functional impairment in cognitive abilities and activities of daily living. The baseline assessment will also include potential moderators of treatment effects for exploratory analyses. We will ask participants who request premature withdrawal from the trial to complete an identical assessment of the major outcomes of interest (ie, self-rated emotion dysregulation, psychiatric symptom severity, cognitive deficits, quality of life, and treatment acceptability) at the time of discontinuation.

#### N-ACT Intervention

##### Overview

The N-ACT program comprises 8 in-person training sessions over 2 months. The intervention is limited to weekly 1 h sessions to maximize adherence and minimize attrition. Each N-ACT session is guided by a trained “coach” (supervised by a licensed clinician) who will explain intervention procedures and rationale, offer relevant psychoeducation, and use motivational interviewing principles to encourage and support participants. At each training session, participants will practice 2 computer-based adaptive tasks targeting affective control. Approximately half of each N-ACT session will be spent performing these exercises, and the other half will be dedicated to coaching and assessment. Coaches will discuss standard cognitive behavioral psychoeducational content regarding emotion regulation (drawn from established therapy protocols).

##### Psychoeducational Content

To begin each weekly N-ACT session, a coach will review information from the previous session and discuss the implementation of learned techniques over the prior week. Coaches will then present information from 1 psychoeducational module, adapted from empirically supported interventions, on the topics presented in Textbox 2. Modules 2 to 7 will also include theoretical justification for cognitive training to enhance emotion regulation.

Topics covered in coaching sessions.
**Coaching session sequence**
Introduction and orientation, which includes an overview of session procedures and program structure, rationale, and personal goal settingCognitive behavioral approaches to emotion, which introduces fundamental concepts derived from cognitive behavioral therapy to elucidate links among affect, cognition, and behavior, plus an emotion regulation strategy (“STOP”) drawn from dialectical behavior therapy (DBT)Environmental influences on feelings, in which participants identify risk and resilience factors that impede or facilitate emotional self-regulation, paired with distress tolerance skill adapted from DBT (“Self-soothing”)Functional analysis of behavior, which involves functional analysis of problematic patterns of thought or behavior related to personal goals for emotion regulationMindfulness, involving a guided meditation practicePsychological flexibility, which introduces key elements of acceptance and commitment therapyInterpersonal skills, covering 2 closely related techniques (also borrowed from DBT) to promote adaptive emotional self-regulation and communication within relationships (“DEARMAN”)Review, summary, and wrap-up, involving an examination of progress toward overarching treatment goals, review of key concepts, and solicitation of participant feedback on program components via interview and self-report

After engaging with psychoeducational content in each module, participants will complete the N-ACT tasks, and coaches will end each session with an informal debriefing to help consolidate learning and identify implementation intentions (ie, interim objectives toward participants’ identified treatment goal) for the coming week. Coaches will additionally administer the PANAS before and after the training tasks. We will audio record N-ACT training sessions (with participant consent) for regular review by independent raters to evaluate coach adherence and fidelity to the intervention guidelines using session-specific standardized forms created for this study.

##### N-ACT Task Battery

#### Overview

Participants will be asked to perform the same 2 computerized training tasks each week, in counterbalanced order: (1) an adaptive emotional n-back (AEnB) task targeting emotional working memory and (2) the ESST-adaptive (ESST-A), which targets emotional response inhibition. These are adaptive versions of the affective control behavioral measures completed during assessment sessions, modified to dynamically adjust the level of difficulty according to participant performance, which we expect to improve with additional training over time. Both training tasks include gamified graphical elements (eg, user-selected avatars) to facilitate user engagement (refer to Multimedia Appendix 1 for task instructions and other details).

#### The AEnB Task

The AEnB training task is an adaptive variant of procedures originally described by Levens and Gotlib [78,79], in which participants are instructed to indicate (as quickly and accurately as possible via keypress) whether a *target* affective picture stimulus is a “match” or a “mismatch” to a *cue* image shown *n* trials earlier, where *n* equals the number of interim trials between the presentation of the original cue and the to-be-evaluated target stimulus (ie, the “n-level”). The AEnB task additionally draws from an adaptive version of the dual-dimension emotional (n-back) working memory training task developed by Pan et al [53], such that cue-target pairs are only considered to match if the images are identical *and* spatially congruent, as each stimulus appears in 1 of 9 positions on an invisible 3×3 grid.

All AEnB task stimuli are pseudorandomly presented and counterbalanced to ensure equivalent numbers of matched and mismatched cue-target image pairs from 3 valence categories (neutral, negative, or positive) within each of 6 blocks, resulting in 36+n trials per block, or 216+n total trials. Image stimuli are shown for 1000 milliseconds on each trial, followed by a 2500-millisecond response window and a feedback screen shown for 1000 milliseconds. Trials are separated by a jittered intertrial interval of approximately 250 milliseconds (150-350 ms) assigned pseudorandomly on each trial.

The AEnB task involves 2 orthogonal adaptive components. The first is a tracking algorithm that adjusts the number of trials per condition (ie, emotional valence of cue-target pairs) to prioritize the encoding of spatial information (over affective content) into working memory for emotionally arousing images. Specifically, independent of the current n*-*level, higher accuracy for emotional (negative or positive) versus nonemotional (neutral) cue-target pairs will result in 2 fewer “match” trial pairs on the subsequent block. Crucially, the emotional images on these 2 trial pairs will remain identical but will be mismatched in spatial location. The algorithm will continue to swap matched emotional pairs with identical mismatched images until the participant achieves greater accuracy for neutral cue-target pairs (that are spatially congruent throughout the task), at which point the number of emotional trial pairs per condition returns to baseline, on a per-block basis, with 1 negative and 1 positive identical but spatially mismatched pair replaced by fully matched emotional cue-target pairs.

The second adaptive feature of the AEnB task is the n*-*level itself, which is adjusted after the first block either upward (n=3) or downward (n=2) at the start of each subsequent block (range: n=1-7), contingent on participants’ accuracy and response times (with larger values indicating greater working memory load). Specifically, the n-level decreases if a participant is unable to achieve at least approximately 80% accuracy (ie, at least 30 correctly identified pairs out of 36+n trials) within a given block; conversely, once a participant surpasses this accuracy threshold, the n-level increases at the start of the next block but only if the mean reaction time during trials with neutral target stimuli is faster than that during trials with emotional stimuli (regardless of whether cue-target pairs are matched or mismatched, provided that responses are accurate). This training approach is intended to encourage the development of relatively more rapid—but equally accurate—evaluative responses to less arousing or salient images. In sum, the AEnB task involves multiple adaptive components designed to facilitate diminished stimulus reactivity or enhanced engagement of affective control when processing emotionally evocative stimuli (eg, via enhanced attentional focus on key perceptual features rather than affective information, per se) for immediate recall in working memory.

#### The ESST-A Task

The ESST-A is a training variant of the original ESST [37,39,43], with comparable design elements; however, the ESST-A is distinct in that emotional (negative or positive) image stimuli are presented exclusively on no-go or stop trials (n=60 per valence), and, conversely, neutral images are only shown on go or no-signal trials (n=90 per block over 4 blocks) without an inhibitory cue. Participants must accordingly terminate emotional reactions to the most arousing and evocative stimuli on the ESST-A. This unique design feature of the ESST-A is meant to facilitate implicit associative learning, wherein salient affective content serves as a reliable “cue” that predicts upcoming stop signals, while stimuli with neutral information are consistently delivered without accompanying inhibitory demand. Therefore, repeated training with the ESST-A is expected to promote more automatic, reflexive engagement of inhibitory control at earlier stages of emotional information processing.

Similar to the nonadaptive version, the ESST-A comprises 4 blocks of 120 trials each, with stimuli presented pseudorandomly and counterbalanced across blocks to ensure equivalent numbers of trials per condition. Each ESST-A trial spans 2000 milliseconds, which includes a fixed pretrial pause period of 500 milliseconds, followed by a central fixation cross displayed for approximately 250 milliseconds, depending on a jittered latency value assigned on a trial-by-trial basis (150-350 ms), comparable to the AEnB task. The target image stimulus replaces the fixation cross in the center of the screen, where it is displayed for 1250 milliseconds. The initial (50 ms) stop signal is presented 250 milliseconds after stimulus onset, separately for positive and negative stimuli.

The primary adaptive component of the ESST-A is identical to the assessment version of the ESST (and similar to other SSTs). Specifically, the ESST-A includes 2 independent staircase algorithms that adjust valence-specific stop-signal delay (SSD) values (ie, distinct tracking values for negative and positive images) in 50-millisecond increments depending on participant performance, such that successful inhibition results in a longer SSD on the next no-go or stop trial with the same type of image, thereby increasing inhibitory demand. By contrast, commission errors (ie, false alarms) shorten each SSD by 50 milliseconds on subsequent no-go or stop trials with images from the same emotional valence category. These 2 stepwise algorithms are programmed to maintain commission error rates at approximately 50% of the no-go or stop trials, separately for negative and positive images, which enables calculation of valence-specific indices of emotional response inhibition (ie, stop-signal reaction time).

#### Data Quality Assurance

The screening survey and assessment questionnaires will randomly incorporate simple “attention checks” (eg, “2 + 2 = ?” and “for our data quality checking, please answer ‘1’ to this question”) to identify patterns of careless responding, which we will supplement by manual review to confirm the validity of self-report data. As previously noted, we will exclude participants who demonstrate patterns of careless responding during the screening questionnaire. Before conducting statistical analyses, research staff will perform comprehensive data cleaning and processing procedures as needed (eg, ascertaining violations of distributional assumptions for parametric tests and comparison with published norms).

#### Training and Reliability

Our team has comprehensive preparation procedures for all staff members involved in data collection. Before study recruitment, N-ACT coaches will receive extensive training in each session-specific intervention module to promote protocol adherence. Coach training and group supervision will comprise regular team-based meetings led by clinically licensed investigators, with didactic instruction, role-play, the development of interrater reliability to evaluate coach fidelity, and a review of practice tapes by senior researchers. We will conduct session adherence evaluations (as a group) monthly and provide retraining as necessary to address drift.

#### Risk Management

##### Overview

Trial procedures are designed to balance respect for participants’ autonomy with the need for safety. Study consent forms will provide contact information for crisis hotlines and other mental health resources. We will offer referral assistance to interested individuals. All team members with direct participant contact will receive training regarding psychiatric emergencies, suicide risk assessment, and crisis management. A detailed manual will provide assessment probes, decision rules, referral resources, and contact information for use during emergency situations. Training will emphasize procedures for providing feedback in a clinically sensitive manner, and senior investigators will use role-play to demonstrate fundamental principles related to assessment, obtaining supervision, providing referrals, and preparing documentation according to legal and ethical guidelines. This training will cover circumstances in which staff are permitted to breach confidentiality to contact emergency services.

Research assistants and coaches will be trained to carefully monitor cues indicating participant distress or discomfort, and we will offer breaks or opportunities to reschedule as warranted for fatigue or distress. Participants who endorse significant distress or endorse active suicidal ideation will be given the opportunity to speak with clinically licensed senior investigators, who will evaluate and determine the need for further follow-up. Research staff will work with these participants to develop a plan to obtain support, which may include strategies for discussing symptoms with their current provider, removing access to lethal means, and the provision of feedback or referrals. Our team has developed relationships with local sites to facilitate referral for individuals with insurance or those without; after referral, we will follow up with these participants as warranted to ensure that they received sufficient support.

##### Adverse Events

We will describe the limits of confidentiality as part of informed consent procedures to minimize the likelihood of study-related adverse events. During the consent process, we will also emphasize that our team is unable to provide emergency services or review research data in real time, and it is therefore important for participants to have access to other sources of care. Consent documents will encourage participants to contact the senior investigators with any concerns.

Throughout the trial, N-ACT coaches will also informally solicit information about potential issues at each training session. We will formally assess adverse events at the postintervention session. We will follow up with participants who show apparent clinical deterioration and will attempt to determine whether emergent symptoms or concerns might be somehow connected to study procedures. Adverse events will be reported to the university’s Committee for the Protection of Human Subjects within 1 week.

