After the baseline assessment (laboratory session, questionnaires, and EMA), we will randomly assign participants to receive active treatment (ie, N-ACT without delay) or the waitlist control condition, unblinded, using an asymptotic maximal procedure to achieve a maximally tolerated imbalance of 2, while maintaining a 1:1 allocation ratio between the 2 trial arms [63]. Participants in the active N-ACT group will begin the intervention, which consists of 8 weekly coached training sessions, within 1 week after baseline EMA. We will recontact waitlist control participants after a period equivalent to the intervention duration (ie, 2 months) to complete a second (postwaitlist) assessment session and EMA before starting the N-ACT program for the following 8 weeks. After the intervention, participants will be asked to complete a second week of EMA, and then a postintervention assessment session with comparable measures to baseline. We will recontact waitlist control participants approximately 10 weeks after their (prewaitlist) baseline assessment session to complete a second (postwaitlist) assessment and 1 week of EMA, parallel with the pre-intervention assessment procedures of the N-ACT group,. The waitlist group will then be offered 8 weeks of N-ACT, followed by a second week of postintervention EMA, and then a final assessment session. In sum, we will follow participants assigned to receive the intervention without delay for 12 weeks (3 mo) and those assigned to the waitlist control group for 22 weeks (5.5 mo). This delayed intervention randomized waitlist-controlled trial design enables us to offer all interested participants the opportunity to participate in the program and maximizes our ability to rapidly accrue a sufficiently sized sample for analyses. Figure 1 demonstrates the flow of potential participants through the study procedures.

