### Ethical Considerations

The University of California Berkeley Committee for Protection of Human Subjects granted approval for this research (2023-01-15949) before data collection. All participants will complete written informed consent before commencing study procedures.

Participants will be assigned an ID number, which will be used in place of their name or other identifying information on all research materials. Data will be kept in secure, password-protected files. Although we plan to make data publicly available for reanalysis, we will carefully deidentify data before doing so. In publishing or presenting the results, we will not provide any information that could identify an individual participant.

Participants will receive course credit or monetary compensation for completing assessment procedures but will not be paid for time spent on screening or the intervention itself. Students will be able to earn credit toward required research hours in their psychology classes. We plan to increase the hourly payment rate slightly over the course of the trial to promote retention, from US $20/h for the baseline assessment to US $30/h for the postwaitlist and postintervention assessments. We will compensate participants up to US $60 (or 3 h of course credit) for completing the baseline assessment (2.5-h in-person session plus 30 min of questionnaires), a US $10 “bonus” for performance on an unrelated computer task during the baseline session, US $10 for each week of EMA if they complete at least 75% of the prompts, and US $60 for the postintervention assessment (1.5-h in-person session plus 30 min of questionnaires). Those randomized to the waitlist control condition will be eligible to receive up to an additional US $60 for completing the postwaitlist assessment (identical to the postintervention assessment).

In sum, participants assigned to complete N-ACT without the waitlist can earn up to US $150 (or 3 h of course credit plus up to US $90), while those in the waitlist control condition could earn up to US $70 in addition to those amounts. Payments will be prorated if participants complete only part of an assessment. We will remunerate participants within 1 week of each completed assessment via digital credit cards, which will be replenished as necessary.

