### Study Procedures

#### Recruitment and Screening

We will invite up to 500 adults to complete preliminary screening procedures and an estimated 100 participants to complete the initial baseline assessment session. After accounting for 20% expected attrition, we expect 40 participants in each condition to complete all study procedures.

Study advertisements will be posted locally in public spaces and distributed by web (eg, via email listserves, Craigslist, and social media sites). We will also administer a prescreening survey to students enrolled in psychology classes at the University of California Berkeley, and we will invite students who meet the preliminary inclusion criteria based on those responses to take part in the study. Potential participants (recruited either from the community or from the student participant pool) will be directed to our website, where they can view additional details about the trial. We intend to recruit only secondarily from the student participant pool to supplement community-based recruitment, which will constitute most of the targeted sample. All questionnaires, including screening items, will be administered through REDCap (Research Electronic Data Capture; Vanderbilt University) software [65], which will also be used for the secure storage of collected data.

After providing informed consent, interested individuals will complete the brief web-based screening via REDCap to assess preliminary eligibility. The inclusion and exclusion criteria are presented in Textbox 1.

Inclusion and exclusion criteria.

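### The only formal adverse-event assessment named is at the postintervention session; the exit assessment for people who withdraw does not list adverse events, and the postwaitlist visit is unclear

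*Protocol article*

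**What the plan says.** All references are to the protocol article.

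- **Adverse Events** names a single formal time point: "We will formally assess adverse events at the postintervention session". It adds an informal route: "N-ACT coaches will also informally solicit information about potential issues at each training session". It also says "We will follow up with participants who show apparent clinical deterioration", and that the team will try to judge whether new problems are linked to study procedures. Events go to the university's ethics committee within a week.
- **Questionnaires** provides for early leavers: "We will ask participants who request premature withdrawal from the trial to complete an identical assessment of the major outcomes of interest". The content is given in a list introduced by *ie*, so it reads as complete: "self-rated emotion dysregulation, psychiatric symptom severity, cognitive deficits, quality of life, and treatment acceptability".
- **Recruitment and Screening** expects about 100 people at the baseline session. "After accounting for 20% expected attrition", it expects 40 per condition to finish all procedures.
- **Ethical Considerations**, in the payment paragraph, speaks of "completing the postwaitlist assessment (identical to the postintervention assessment").
- **Methods, Overview** describes the same postwaitlist visit as "parallel with the pre-intervention assessment procedures of the N-ACT group".

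**The concern.** This is an early test of a new intervention in people selected for emotion dysregulation, and the plan intends to judge whether worsening is connected to the study. That judgement needs events from people who leave as well as from those who stay, because worsening is one possible reason for leaving. The plan already arranges a contact at withdrawal, but by its own list that contact does not ask about harms.

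The second issue is the reference period. Some worsening is expected in this population without any intervention, and the waiting period is the only randomised yardstick for it. To serve that purpose, the waitlist arm must be asked the same question in the same way at the end of the wait. The text does not make clear that it is.

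**Working it through.** **1. Reproduce the plan's recruitment figure.** Inputs from Recruitment and Screening: 80 completers (40 per arm) and 20% attrition.

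80 / (1 − 0.20) = 100, which matches the stated number at baseline. With 1:1 allocation (Methods, Overview), and if all 100 are randomised, there are 50 per arm.

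**2. How many could lack a formal record.** 50 − 40 = 10 per arm, or 20 of 100. This is a ceiling at the planned attrition, for two reasons. Randomisation follows the baseline questionnaires and the week of momentary assessment, so some of the 20% may be lost before allocation. And the 40 are people completing *all* procedures, so someone who misses training sessions can still attend the postintervention session and be asked.

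**3. What that could hide, without assuming anything about those who leave.** If x events are seen in 40, the proportion among all 50 lies between x/50 (no unseen participant had an event) and (x + 10)/50 (all did). The article gives no event rate, so the values of x are illustrative.

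| Seen | Rate among 40 | Possible range over 50 |
|---|---|---|
| 0 | 0% | 0% to 20% |
| 2 | 5% | 4% to 24% |
| 4 | 10% | 8% to 28% |

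**4. Sampling precision alone.** With zero events in n people, the one-sided 95% upper limit is 1 − 0.05^(1/n). For n = 40 this is 7.2%; for n = 50 it is 5.8%. The gain in precision from adding early leavers is small. The reason to add them is step 3: the 7.2% limit says nothing about people who were not asked.

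**5. The waitlist arm, side by side.**

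| Source | Nature of the postwaitlist visit | Formal adverse-event enquiry at T2? |
|---|---|---|
| Ethical Considerations | Identical to the postintervention assessment | Yes, if read literally |
| Methods, Overview | Parallel with pre-intervention procedures | No, if read literally |
| Adverse Events | Not mentioned | Not stated |
| Table 1 | Same core measures ticked as after training | Not settled: adverse events have no row |

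On the second reading, waitlist participants are first formally asked after their own training, in a follow-up of 22 weeks, and someone who completes the wait but declines training is never formally asked.

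**6. Informal enquiry between T1 and T2.** Immediate arm: up to 8 coached sessions, each with an informal question. Waitlist arm: no sessions in that period, and no scheduled enquiry is described.

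**The case against.** The strongest reply is that harms in early leavers are not wholly unrecorded. A participant in training has been asked informally at every session attended. Follow-up of deterioration is not limited to completers or to one arm. Staff are trained to watch for distress, and participants are encouraged to contact the senior investigators. The exit assessment includes symptom severity, so worsening would show among those who complete it. All of this stands and narrows the gap. It does not close it: a symptom score does not record an event, its date or its possible link to the study, and Adverse Events says that research data are not reviewed in real time.

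A second reply is that the exit list concerns outcomes, and that a safety question at withdrawal may sit in the full protocol or the staff manual. That is possible. But the article does state where the formal assessment takes place, and it does define the exit content, so following the text as written leaves early leavers without the form.

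A reader might go further and infer that the trial has no comparable waitlist data on harms, or that its harm rate will describe completers only. The documents do not support either. The payment paragraph and Table 1 favour an equivalent postwaitlist visit, so the waitlist point is an ambiguity. The article plans no adverse-event rate and no between-arm test of harms, so there is no stated analysis to call biased. Nor does it give an event rate for people who leave; a percentage understatement could only rest on a guessed multiplier, and none is claimed here.

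**Conclusion.** The point holds in a limited form. One formal adverse-event assessment is named, and the exit assessment, as listed, leaves adverse events out. Up to about 10 of 50 participants per arm could have no formal record, assuming that all 100 at baseline are randomised, that attrition is the planned 20%, and that nobody counted as lost attends the postintervention session. At that ceiling, an observed 0 of 40 is compatible with anything from 0% to 20% of the arm. Informal routes reduce the practical loss by an amount that the article does not allow one to estimate.

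For the waitlist arm, two descriptions of the same visit disagree and need reconciling. Even on the favourable reading, scheduled informal enquiry is unequal between arms from T1 to T2, so events raised that way are not comparable between arms.

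**What to change.** 1. In Questionnaires, add an adverse-event form to the assessment at discontinuation, the same form as at the postintervention session.
2. In Adverse Events, name the postwaitlist assessment alongside the postintervention session, and make the descriptions in Methods, Overview and Ethical Considerations agree with it.
3. State that formally collected events will be reported by randomised arm from T1 to T2 for all randomised participants, with the number in each arm who were never formally asked.
4. List events raised informally with coaches separately, outside any comparison between arms.

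This uses contacts that already exist and needs a few minutes per participant plus a wording change. The exit questionnaire becomes slightly longer, and the count of harms may look less favourable. It will not reach people who leave without requesting withdrawal, so the number formally asked would move toward 50 per arm but may not reach it. The change is best made before anyone leaves the trial, because events not asked about at exit may not be recoverable later.
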